## Abstract

**Background:**

There is a need for efficient and engaging strategies that will mitigate the effects of aging on cognitive and physical functions while keeping users motivated for long-term adherence.

**Objective:**

This study protocol is designed to investigate, in older adults, the advantage of integrating cognitive training with aerobic exercise (AE) in fun group sessions to potentiate the effect of training on cognition while improving physical function. The protocol explores the effects of a novel intervention, the Activ4Brain program, on cognition and physical function as well as the underlying neurobiological mechanisms.

**Methods:**

The program consists of group AE classes that include computerized games designed to train cognition during exercise, taking advantage of exercise-induced arousal. Cognitive training task difficulty is adapted throughout the intervention as users improve their performance. Importantly, the setup allows for simultaneous body movements to maintain aerobic activation. This is a 3-arm controlled trial, using a parallel design with a 1:1:1 allocation to an experimental group that is engaged in the Activ4Brain program (24 sessions, twice a week), an active control group that is engaged in AE sessions, and a passive control group. Participants are tested at baseline and after the intervention. The main study outcome is changes in cognition. Additional outcomes include changes in brain and autonomic function, levels of inflammation and neuroprotective markers, cardiovascular and physical functional fitness, and body composition.

**Results:**

Data collection started in January 2024 and finished in April 2025. Seventy-three individuals (40 women and 33 men) were enrolled in the study and assigned to the 3 groups. The average age was 66 (SD 6) years. Data analyses are ongoing, with the publication of the results estimated for 2026 and 2027.

**Conclusions:**

This study will produce knowledge important for the development of efficient strategies to fight age-related decline.

## Introduction

Cognitive training holds the potential to be a successful nonpharmacological treatment for age-related cognitive decline and dementia. However, there is a need for the design of better tools, as existing interventions show little to no benefit for preventing or delaying cognitive decline [1]. Similarly, physical exercise has been explored as an intervention for improving cognitive function. However, although in patients with mild cognitive impairment the cognitive effects of exercise are positive [2], in the general population the effects are small, suggesting caution in the use of exercise for prevention of age-related cognitive decline [3].

Despite these shortcomings, physical exercise can be used synergistically with cognitive training to boost their effects on cognition. Exercise increases arousal and potentiates neurogenesis and neuroplasticity through the release of brain-derived neurotrophic factor [4,5]. Thus, enhancing brain arousal before and during cognitive training might be beneficial because the brain will be more apt to attend to the information presented (enhanced arousal) and to learn and consolidate new skills (enhanced synaptic plasticity). Moreover, learning plays an important role in promoting neuroplasticity and the survival of neurons [6]. Therefore, adding cognitive challenges to periods of physical activity may maximize the benefits of exercise on cognition. Another reason why it is beneficial to include exercise in a program tackling cognitive decline is that exercise engages the noradrenergic system, one of the neural systems associated with the arousal response. Noradrenaline has a protective role against the onset and progression of cognitive decline [7-9], probably through its anti-inflammatory role [10]. Repeated activation of the noradrenergic system during regular exercise sessions might lead to beneficial permanent changes in the structure, connectivity, and function of the noradrenergic system, leading to improved brain function and brain health.

Taking into consideration the synergy between physical activity and brain function, we designed the program Activ4Brain as a nonpharmacological strategy to reduce the impact of age-related cognitive decline. Previous studies have explored the use of simultaneous physical exercise and cognitive training [11]. Exergames are commonly used in this type of intervention; however, the difficulty to adapt to the needs and abilities of the study participants limits their capability to address specific cognitive difficulties [12-15]. Other studies use single cognitive tasks, thereby training a very limited set of cognitive skills [16], or use designs that do not adapt task difficulty as the participants improve their performance during the intervention, an important feature to optimize learning [17,18]. Our novel program was designed to address these limitations. The Activ4Brain program consists of group aerobic exercise (AE) classes that include simultaneous computerized tasks designed taking into consideration the cognitive domains that respond to training and are more affected by aging, and the best practices for inducing long-lasting brain and behavioral plasticity [19,20]. During AE classes, visual stimuli are displayed on a screen at the front of the room, and the participants are instructed to respond according to the cognitive training tasks’ rules using foot pedals, while standing and moving their bodies to maintain arousal levels throughout. In this way, this program integrates cognitive training in AE. Task accuracy is automatically recorded, and the tasks’ difficulty levels are adjusted weekly to ensure participants are challenged by the cognitive training tasks throughout the intervention. The program consists of 24 sessions, held twice a week. Each session is 50 minutes long, during which 5-minute bouts of AE (used to increase arousal levels) alternate with 5-minute bouts of cognitive training. The program Activ4Brain is designed to be applied in group classes in a dynamic and fun manner at the sound of music, promoting social interaction (an important factor for successful aging), increasing its user motivation and long-term adherence, and facilitating its application on a large scale.

This study protocol was designed to assess the cognitive impact of the Activ4Brain program and to elucidate the neural and biochemical mechanisms underlying its effects. Participants are tested at baseline and after the 3-month intervention. Participants are assessed for cognitive function using a comprehensive cognitive assessment protocol including memory and executive function tests. This is our main outcome. To examine brain and autonomic function, we acquire the electroencephalogram (EEG), the pupilogram, and the electrocardiogram (ECG) during rest and while participants are engaged in a value-based learning task (reinforcement learning task). Reinforcement learning is a skill that is impaired in older people [21], involves the engagement of the arousal system [22], and depends on executive function [23]. We hypothesize that training executive function will result in improvements in reinforcement learning, thereby asserting transfer learning to untrained tasks. These analyses will elucidate if the Activ4Brain program induces changes in brain and autonomic activity during rest and cognitive task performance and behavioral improvements in untrained tasks (far transfer) and will facilitate the investigation of the neurobiological mechanisms that underlie the cognitive changes. To investigate if the relationship between exercise and improved cognition is linked to a reduction in inflammation and an enhancement in neuroprotection, we also measure inflammatory and neuroprotective blood markers. To examine the program’s impact on physical health markers, we assess body composition, physical functionality, and physical and cardiovascular fitness.

## Methods

### Trial Registration and Protocol Timing

As a behavioral, nonpharmacological intervention aimed at improving cognitive health and well-being in aging, prospective registration was not initially anticipated by the authors, and the study was registered on ClinicalTrials.gov (NCT07108413) only after completion of data collection. Data collection started in January 2024 and finished in April 2025. The protocol registration was submitted in July 2025 and published in August 2025. The aim of this retrospective trial registration and publication is to document this extensive protocol in detail, including a novel intervention. This will allow the protocol to be reproduced, and it will assist with the reporting of the results that will be divided into several publications focused on the analyses of the different outcomes and different aspects of the intervention.

No public involvement is planned for any stage of the study, including in the protocol design.

### Study Design and Intervention Protocol

Our study consists of a 3-arm controlled trial with a parallel study design involving cognitively healthy older people. Participants are allocated into the Activ4Brain group and 2 control groups: an active control group engaged in AE alone and a passive control group, instructed to maintain their daily routines. The passive control group is included to control for the effect of test-retest. The AE group is included to assess if including cognitive training leads to a greater effect on cognition than AE alone and to control for the participants’ motivation to engage in the evaluation sessions, which might be decreased in passive control groups. The group allocation ratio is 1:1:1. The intervention consists of 24 sessions, held twice a week for 3 months. The participants are tested at baseline and after the 3-month training programs (Figure 1).

**Figure 1. F1:**
[figure not shown]
Study flowchart. The research protocol is divided into 3 main parts. Part 1, with a duration of 1 month, corresponds to the initial data collection phase (T0), serving as the baseline assessment. Part 2 corresponds to the 3-month intervention protocol, which includes the Activ4Brain program (Activ4Brain group) and the aerobic exercise-only program (AE group). Part 3, with a duration of 1 month, corresponds to the follow-up data collection phase (T1) conducted after the intervention.

### Ethical Considerations

The study protocol was approved by the Faculty Ethical Committee of the Faculty of Sports Science and Physical Education of the University of Coimbra with the reference number CE/FCDEF-UC/00082023. All participants are asked to read and sign a consent form. This protocol is reported in accordance with the SPIRIT (Standard Protocol Items: Recommendations for Interventional Trials) 2025 guidance (see Checklist 1 for a completed checklist). The results will be reported following the CONSORT (Consolidated Standards of Reporting Trials) extension for nonpharmacological interventions [24].

### Participant Recruitment, Eligibility Criteria, and Sample Size

Participants are recruited from Portugal’s Coimbra District through personal communications, press releases, social media posts, and distribution of informative leaflets and posters. Recruited participants receive comprehensive information regarding data collection procedures, exercise protocols, and measures of protection of personal information procedures. Participants who volunteer to participate in the study are interviewed for eligibility and asked to sign an informed consent form.

Inclusion criteria are cognitively healthy men and women between 55 and 75 years of age, with a physical condition compatible with the practice of moderate AE. Exclusion criteria include any disability or health problem incompatible with moderate AE and objective cognitive impairment. The Physical Activity Readiness Questionnaire is used to screen contraindications for physical exercise. Before the intervention, we ensure participants’ fall risk is low using the Timed Up and Go (TUG) test [25].

Participants are instructed to continue any ongoing concomitant care. Details of the concomitant care received are recorded at baseline and, to assess any changes, at follow-up.

Sample size determination has been made using the G*power (version 3.1.9.7; written by Franz Faul, Universität Kiel, Germany) program. As reported in previous studies [26,27], we expect a small to moderate effect size of the Activ4Brain program on cognitive function (our primary end point). We calculated a sample size of 66 participants by setting Type I error (α) at 0.05, Type II error rate (1−β) at 0.95, and an effect size η^2^ of 0.06 (corresponding to an effect size *f* of 0.25, using the option for effect size specification as in G*Power 3.0) for repeated-measures ANOVA, within-between interaction, with 3 groups and 2 repeated measures. Accepting a dropout rate of 10%, 75 participants are recruited.

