### Statistical Analysis Plan

The study of the effect of the Activ4Brain program on the primary outcome (cognitive function) is confirmatory because we hypothesize, according to previous evidence, that the integrated cognitive-aerobic training program results in larger improvements than AE alone or no intervention (passive control) [47]. All other analyses are exploratory.

Continuous cognitive outcomes will be summarized descriptively with mean (SD) for each group and time. These variables will be analyzed with repeated-measures ANOVA with 1 between-subjects factor (group) and 1 within-subjects factor (time=preintervention vs postintervention). The Activ4Brain intervention will be considered effective in improving cognitive function if the group × time interaction is significant at a level of .05, if the post hoc tests (with CI adjustment using Bonferroni) show a significant effect of time for the Activ4Brain group, and the improvement is higher for this group than for the other control groups. If the data do not meet assumptions of sphericity, the Greenhouse-Geisser correction will be used. Description of the effect sizes by partial η^2^ will follow the following cutoff points: less than 0.06 will be considered a small effect; between 0.06 and 0.14 will be considered a medium effect; and higher than 0.14 will be considered a large effect [48].

Missing data will be assessed prior to analysis. Analyses will be conducted using the available data (complete case analysis), and participants with missing data for a specific outcome variable will be excluded only from the relevant analysis.

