## Results

Data collection started in January 2024 and finished in April 2025. Seventy-three individuals (40 women and 33 men) were enrolled in the study and assigned to the 3 groups. The average age was 66 (SD 6) years. Data analyses are ongoing, with the publication of the results estimated for 2026 and 2027.

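### The 95% power at N = 66 is for an interaction partial η² of about 0.20, which the trial's own cutoffs call large; at partial η² 0.06 power is about 42%

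*Protocol article*

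**What the plan says.** In Participant Recruitment, Eligibility Criteria, and Sample Size, the protocol article gives the expectation first: "we expect a small to moderate effect size of the Activ4Brain program on cognitive function (our primary end point"). The inputs follow: "setting Type I error (α) at 0.05", "Type II error rate (1−β) at 0.95" and "an effect size η^2^ of 0.06", the last equated with f = 0.25, "using the option for effect size specification as in G*Power 3.0) for repeated-measures ANOVA, within-between interaction, with 3 groups and 2 repeated measures". The test is thus the group-by-time interaction, and the result is 66 participants, raised to 75 for 10% dropout. No pre-post correlation is given.

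The Statistical Analysis Plan section tests the same interaction and reports its size as partial η². Below 0.06 is small; "between 0.06 and 0.14 will be considered a medium effect; and higher than 0.14 will be considered a large effect".

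The Study Outcomes section and the Discussion both say that the trial is powered for cognitive function. The Statistical Analysis Plan section calls that analysis confirmatory.

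**The concern.** Read together, the two sections suggest that the trial has 95% power at the boundary between a small and a medium effect. The value 0.06 appears in both, once as a planning input and once as a reporting cutoff, but it does not mean the same thing in each. Under the named option, f is scaled to the SD of a single measurement, and the program then multiplies f² by the number of measurements over one minus the correlation. The partial η² that the analysis will report is on the scale of the change scores. If the two scales are far apart, a non-significant interaction would be taken as strong evidence against a moderate benefit when the design could easily have missed one.

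**Working it through.** **Inputs.** From the article: α = 0.05, power 0.95, f = 0.25 (η² = 0.06), k = 3 groups, m = 2 measurements, N = 66, 73 enrolled, and partial η² cutoffs of 0.06 and 0.14. Assumed: pre-post correlation ρ, which is not stated and is varied below.

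**1. Reproduce 66.** Under the named option, λ = N·m·f²/(1 − ρ), with (k − 1)(m − 1) = 2 and N − k = 63 degrees of freedom.

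- With ρ = 0.5: λ = 66 × 2 × 0.0625 / 0.5 = 16.5. The critical F is 3.143 and power is 0.953. The smallest N divisible by 3 that reaches 95% is 66.
- A simulation of this case (20,000 runs) gave 0.955.
- Other correlations do not give 66: ρ = 0 needs 129, ρ = 0.3 needs 90 and ρ = 0.7 needs 42.

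**2. Put that input on the reporting scale.** The option multiplies f² by m/(1 − ρ) = 2/0.5 = 4. On change scores f² = 4 × 0.0625 = 0.25, so f = 0.50 and partial η² = 0.25/1.25 = 0.20. The trial's cutoffs call this large.

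**3. Put it in SD units.** The SD of the three group mean changes is 2f = 0.5 baseline SD. If only Activ4Brain differs, with advantage d over both controls, the SD of (d, 0, 0) is d√2/3 = 0.4714d. Hence d = 0.5/0.4714 = 1.06 SD.

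**4. Work on partial η² throughout.** Here λ = N × η²p/(1 − η²p), and ρ drops out.

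| Question | Result |
|---|---|
| λ needed for 95% power, N = 66 | 16.2 |
| Partial η² for 95% power, N = 66 | 16.2/(16.2 + 66) = 0.197 |
| Power at 0.06, N = 66 (λ = 66 × 0.06/0.94 = 4.21) | 41.7% |
| Power at 0.06, N = 73 (λ = 73 × 0.06/0.94 = 4.66) | 45.7% |
| N for 80% power at 0.06 | 156 |
| N for 95% power at 0.06 | 246 |

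A variant of the formula, λ = f²(N − 3), moves these only slightly: partial η² 0.205 for 95% power, and 40% power at 0.06.

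**5. SD-based figures over a range of ρ (N = 66, only Activ4Brain differs).** The SD of change is √(2(1 − ρ)) baseline SD. The advantage detectable with 95% power is d = √(0.2455 × 2(1 − ρ))/0.4714, where 0.2455 = 16.2/66 before rounding.

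| ρ | Advantage for 95% power | Omnibus power for a 0.5 SD advantage |
|---|---|---|
| 0 | 1.49 SD | 20% |
| 0.3 | 1.24 SD | 27% |
| 0.5 | 1.05 SD | 37% |
| 0.7 | 0.81 SD | 57% |
| 0.8 | 0.66 SD | 76% |

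The 1.05 SD here and the 1.06 SD in step 3 differ because 66 gives 95.3% power, not exactly 95%.

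**The case against.** The best defence is that nothing was miscalculated. The article names the software option, η² 0.06 does convert to f 0.25, and with ρ = 0.5 that f has 95% power on the option's own scale. The sample size section also writes η², not partial η². All of this stands. A reader might infer that 66 is an arithmetic error, or that the 95% is false on every scale; the document supports neither reading. What remains is that partial η² is the only scale the article gives for interpreting this interaction, that 0.06 is one of its cutoffs, and that nothing warns the reader that the planning value lies elsewhere.

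A second defence is that the consequence in SD units depends on ρ. That is right: at ρ = 0.8 a 0.5 SD advantage has 76% power. SD-based statements therefore need a range. The partial η² figures do not.

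The expectation of a small to moderate effect rests on cited studies that are not available here, so their scale cannot be checked. The investigators may keep the expectation; what they cannot do is present it as the effect the design is powered for.

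A reader might also infer that the trial fell short because 73 less 10% is 65.7. This has no weight: the 10% is a planning allowance, not observed attrition, and power at N = 65 is still 0.950. Nor is 75 an error: 66/0.9 rounds up to 74, and 75 is the next multiple of 3. Writing Type II error rate for 1 − β is a slip of wording that changes no figure.

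Finally, data collection is over, and the Discussion says the results will mainly generate hypotheses. But it also keeps the primary comparison as confirmatory, and results are still to be published, so the power statement will still shape how a null result is read.

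**Conclusion.** The power statement is wrong as written on the trial's own reporting scale. With 66 completers the design has 95% power for an interaction partial η² of about 0.20, a large effect by the article's cutoffs, and about 42% at 0.06 (about 46% at 73). These figures rest on the noncentral F for three equal groups and two time points and do not depend on the correlation. Two things do depend on it: that f = 0.25 yields 66 and equals partial η² 0.20 (ρ = 0.5, inferred because only about that value reproduces 66), and every statement of a detectable advantage in SD. The fault is one of effect-size scale and labelling, not of calculation.

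**What to change.** Leave N unchanged and correct the text of the sample size section:

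- State the effect-size scale and the assumed correlation. Suggested wording: *With 66 completers, α 0.05 and an assumed pre-post correlation of 0.5, power is 95% for an interaction partial η² of about 0.20 (about 1.06 SD greater change than both controls if only Activ4Brain differs) and about 42% for 0.06.*
- Give the detectable advantage over a range of correlations: about 1.49 SD at 0, 1.24 at 0.3, 1.05 at 0.5, 0.81 at 0.7 and 0.66 at 0.8.
- Do not describe the powered effect as small to moderate. The investigators' expectation may stay, marked as an expectation.
- Replace the Type II error label with power.
- In the Statistical Analysis Plan section, say that non-significant results will be interpreted with confidence intervals on the pairwise differences in change.

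The cost is a text correction, with no extra participants or data. The downside is that the stated power becomes less favourable.

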### Study Outcomes

#### Assessment Procedures

Study outcomes are assessed at baseline and after the end of the intervention period (3-mo follow-up). Each assessment time point comprises 4 facility-based visits: (1) cognitive assessment (2 h), (2) EEG, pupil, and ECG recording session (2 h), (3) physical evaluation session (30 min), and (4) blood collection. Participants from the Activ4Brain group attend an additional visit to be assessed on the cognitive training tasks used in the program (30 min). The testing sessions end prematurely if the participants show signs of fatigue. Participants are informed of the preparation requirements, which will be checked prior to the assessments.

The study is designed to be powered for the primary outcome only (cognitive function). All secondary and other outcomes—brain and autonomic function (EEG, pupil, ECG), inflammatory and neuroprotective markers, physical fitness and body composition, feasibility and usability, and analyses of the associations between changes in these markers and changes in cognitive function—are exploratory. They are not individually powered and are intended to generate new hypotheses and inform the design of future, adequately powered studies.

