The retrospective nature of the publication of this protocol has the objective of providing a detailed description of the methods, ensuring that the information is available for trial replication. However, due to the inherent limitation associated with the fact that the publication of the protocol occurred after the end of data collection and the analysis plans presented were not specified before the data were acquired, the results from the study will be used mainly to generate new hypotheses for future clinical trials. Nevertheless, we expect that integrated cognitive and AE will have a stronger effect on cognition than AE alone [47], and we will treat this analysis as confirmatory. However, it is important to note that we are studying the effects of a novel intervention designed specifically for this study, and we do not have strong convictions regarding which specific cognitive domains will be most affected and which cognitive tests will best capture these effects, particularly when addressing cognitive decline in healthy older people. In fact, a large percentage of studies investigating the impact of this type of intervention on cognition use measures of global cognition such as the Mini-Mental State Examination or the Montreal Cognitive Assessment. These tests, while adequate to help diagnose mild cognitive impairment and dementia, suffer from ceiling effects in the cognitively healthy population [62]. To avoid this problem, this protocol includes measures of cognition more sensitive to subtle changes in cognitively healthy older adults.

Notably, it is possible that this type of intervention might be particularly effective in people with lower physical function and/or lower cognitive function who present a higher potential for improvement. In fact, there is evidence that age-related cognitive decline shows high variability, with some individuals aging better than others [63]. Future studies should explore the impact of the intervention focusing on populations with sedentary lifestyles, lower education levels, or poorer cognitive function.

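### The stated 95% power is for the three-arm omnibus interaction; it is not the power to show that Activ4Brain beats aerobic exercise (AE) alone, a necessary part of the confirmatory question

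*Protocol article*

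**What the plan says.** The sample size paragraph (Participant Recruitment, Eligibility Criteria, and Sample Size) sizes the trial on one test, "for repeated-measures ANOVA, within-between interaction, with 3 groups and 2 repeated measures". The inputs are "setting Type I error (α) at 0.05", "Type II error rate (1−β) at 0.95" (1−β is power, so 95% power is meant) and f = 0.25, "using the option for effect size specification as in G*Power 3.0". The result is 66 participants, raised to 75 for 10% dropout.

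The confirmatory question is stated in terms of comparators:

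- Study Design and Intervention Protocol: "The AE group is included to assess if including cognitive training leads to a greater effect on cognition than AE alone". The passive arm is there to control for retest effects.
- Statistical Analysis Plan: the confirmatory hypothesis is that "the integrated cognitive-aerobic training program results in larger improvements than AE alone or no intervention (passive control"). Success needs a significant interaction, a significant time effect for Activ4Brain in Bonferroni-adjusted post hoc tests, and a higher improvement than in the control groups.
- Discussion: "we expect that integrated cognitive and AE will have a stronger effect on cognition than AE alone", and this analysis is to be treated as confirmatory.

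Assessment Procedures says "The study is designed to be powered for the primary outcome only (cognitive function"), and the end of the Discussion repeats that the sample size was set for that outcome. The article gives no power or detectable difference for Activ4Brain versus AE.

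**The concern.** An omnibus group × time test with three arms asks whether the mean changes differ anywhere. If both exercise arms improve and the passive arm does not, the test can be significant with little separation between Activ4Brain and AE. Its power is therefore not the power to show that cognitive training adds something to AE.

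That added value is what the AE arm was included to test, and the Discussion singles it out. A reader who sees 95% power and a study described as powered for cognition will naturally apply that figure to the AE comparison. If that comparison is then non-significant, the reader may conclude that the training adds nothing, although the design may have had only moderate power to show it.

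**Working it through.** **Inputs from the article.** N = 66, so 22 per arm at 1:1:1; f = 0.25 under the G*Power 3.0 specification; α = 0.05; power 0.95; k = 3 groups; m = 2 measures.

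**Assumptions not in the article.**

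- Pre-post correlation ρ = 0.5, chosen because it reproduces the stated N. With ρ = 0.3 the balanced N is 90, and with ρ = 0.7 it is 42.
- Bonferroni over three pairwise comparisons, so 0.05/3 = 0.0167 two-sided.
- The position of the AE mean change between passive control and Activ4Brain.

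**Step 1. The plan's own figure.** λ = f²·N·m/(1−ρ) = 0.0625 × 66 × 2 / 0.5 = 16.5. The noncentral F with 2 and 63 df at α = 0.05 gives power 95.3%. The minimum N is 65, or 66 when balanced, so the stated sample size is correct for the test named.

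**Step 2. What this implies for the arm means.** On change scores, λ = n·Σ(deviation of arm mean from the overall mean)², in units of the SD of change. The sum of squares is 16.5/22 = 0.75. Let passive = 0, Activ4Brain = g and AE = x·g. Then (2/3)·g²·(1 − x + x²) = 0.75, so g = √[1.125/(1 − x + x²)]. The Activ4Brain–AE difference is d = (1 − x)·g. Any x is compatible with λ = 16.5, so the plan's inputs fix the omnibus power but not d.

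**Step 3. Power for Activ4Brain versus AE.** Two-sided noncentral t, 63 df (pooled error), noncentrality d·√(22/2):

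| AE share of the Activ4Brain gain (x) | g | AE gain over passive | d | Power at 0.05 | Power at 0.0167 |
|---|---|---|---|---|---|
| 0 | 1.06 | 0 | 1.06 | 93.4% | 85.2% |
| 1/3 | 1.20 | 0.40 | 0.80 | 74.5% | 58.1% |
| 1/2 | 1.22 | 0.61 | 0.61 | 51.6% | 34.1% |
| 2/3 | 1.20 | 0.80 | 0.40 | 25.8% | 13.7% |

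Omnibus power is 95.3% in every row.

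**Step 4. The success rule as a whole.** By simulation (200,000 runs or more per scenario):

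- If Bonferroni-significant superiority over both controls is required as well as a significant interaction, power is 76%, 57%, 34% and 14% for the four rows.
- If the improvement need only be numerically highest, alongside a significant interaction and Activ4Brain time effect (passive change taken as zero), power is about 94% to 95% in the first three rows.

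**Step 5. Detectable difference at 22 per arm.** For 95% power, d ≈ (t critical value + 1.645)·√(2/22). Unadjusted, this is (1.998 + 1.645) × 0.3015 = 1.10 SD of change. With Bonferroni it is (2.460 + 1.645) × 0.3015 = 1.24, or 1.25 from the exact noncentral t.

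**The case against.** - **The sample size is not wrong.** A reader might infer an arithmetic error. There is none: 66 reproduces, the article names the test it powers, and that test is the first condition of the success rule. This stands. The issue is what the 95% may be taken to cover.
- **AE is not the only confirmatory comparator.** The Statistical Analysis Plan section also names passive control, and only the Discussion singles out AE. This stands too. AE is a necessary part of the confirmatory question, not the whole of it.
- **The lower figures come from chosen scenarios.** A reader might infer that the trial has only 34% power, or that its power lies between 34% and 85%. The article supports neither. The half-gain case needs an AE gain of 0.61 SD of change over passive, which sits badly with the Introduction's view that exercise effects on cognition in the general population are small. If small is taken as 0.2 SD (an assumption), power at the same omnibus effect is 87% unadjusted and 75% with Bonferroni; at 0.3 SD it is 82% and 67%. Equally, 34% is no floor, as the two-thirds row shows. If AE did worse than passive by the full Activ4Brain gain, Bonferroni power would be 94%.
- **The rule may ask only for a numerically higher improvement.** The wording allows this, and power then stays near 94% to 95% in the first three scenarios. But a numerical lead would not demonstrate superiority over AE, so this reading does not rescue the claim.
- **Enrolment exceeded 66.** With 73 enrolled and 10% dropout, 73 × 0.9 = 65.7 remain, so 22 per arm is a fair planning figure. Even 25 fully analysed per arm gives only about 90% (AE equal to passive) or 39% (half the gain) with Bonferroni.
- **Practical effect is limited.** Data collection is over, and the Discussion says the results will mainly generate hypotheses. That lowers the stakes, but the same paragraph keeps the AE comparison confirmatory.

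**Conclusion.** The point holds as one about which test the 95% describes. That figure belongs to the three-arm omnibus interaction and cannot be carried over to Activ4Brain versus AE, whose power the article's inputs leave undetermined. In the four scenarios the shortfall against 95% runs from about 2 points (AE equal to passive, no adjustment) to about 81 points (two thirds of the gain, Bonferroni). Even the most favourable of the four does not reach 95%.

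The figures rest on ρ = 0.5, 22 analysed per arm, pooled error variance, three-pair Bonferroni where stated, and the assumed pattern of arm means. The conclusion that 95% is not the power of the AE contrast does not depend on a particular pattern; the size of the gap does. The statements that the study is powered for cognition therefore need qualifying.

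**What to change.** 1. In the sample size paragraph, state that 95% applies only to the three-group omnibus interaction, and give the assumed pre-post correlation. Add either the power of Activ4Brain versus AE on change at 22 per arm under stated AE assumptions, or the detectable difference (about 1.10 SD of change unadjusted, or 1.25 with three-pair Bonferroni, for 95% power).
2. In Assessment Procedures and at the end of the Discussion, qualify the statements that the study was sized for cognition in the same way.
3. Report the Activ4Brain–AE difference in change with its confidence interval, and say that a non-significant result there will not be read as evidence of no added benefit.
4. Keep the announced Bonferroni adjustment. Relaxing it would recover power, but doing so after data collection, with five primary cognitive domains, is a debatable trade-off and is not needed to correct this point.

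The cost is some rewording and one short calculation, with no new participants or data. The downside is a less favourable stated power for the AE comparison.
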